#### Music stimulation

Music stimulation will consist of passive listening to 8 musical tracks. Four tracks will be chosen based on the musical preferences of each patient. Preferences will be derived from a musical anamnesis, namely a structured interview with the caregiver to know the patient’s lifestyle history and musical taste, conducted by the neuropsychologist. The outcome of this interview will help to tailor an individual treatment with familiar and self-relevant music, as previously done [47, 48]. The other four tracks are fixed and chosen by us based on previous literature: Adios Nonino by A. Piazzolla (used in several brain imaging studies); the Prelude in C major by J. S. Bach and the Prelude in C minor from the “Well-tempered Clavier”–I vol.; and a “atonal” version of the C major Prelude (also from the “Well-tempered Clavier”) where the original interval relationships between each note have been altered while maintaining the ascending/descending trend and temporal values of the notes. The two preludes and the atonal version have been used in previous neurophysiological and behavioural studies of auditory memory in healthy and elderly adults [49–52]. For optimising the stimulus variation, the eight tracks will be organized in playlists always alternating based on familiarity (the favourite song alternates a fixed one), on acoustic features (e.g., a track containing lyrics alternates an instrumental one) and emotional content (an arousing track alternates a relaxing one).

All patients will undergo standard physiotherapy rehabilitation treatment, according to the hospital guidelines, for one hour a day, 5 days a week. In addition, most of these patients are treated with specific drug therapy (such as, amantadine, citicoline, dopamine, etc.) in order to increase the level of consciousness. During data analysis these aspects will be considered and treated as necessary. Specifically, drug treatment and doses will be inserted as confounding factors and covariates in the ANOVAs.

### Experimental design and procedures

The experimental paradigm is one of the main strengths of the study, as a randomized cross-over design will be used in this trial, including a treatment condition with electric brain stimulation combined with music listening and a placebo condition with sham brain stimulation combined with noise listening. The randomization of the participants to be included in each group will be done using the software “Research Randomizer” (www.randomizer.org). The randomization procedure will be performed by an independent researcher unrelated to the study. The randomization file will be saved in a password-protected online database. This independent researcher will enrol participants and will assign the patients to intervention groups. Both patients and examiner will be fully blinded.

Assessment times of outcome measures will be conducted at admission (T_0_), after the first weeks of post-intervention or post-placebo (T_1_), and after the second two weeks of post-intervention or post-placebo (T_2_) (Fig 1). Patients will be randomized into three groups depending on the order of the stimulation or placebo conditions:

Stimulation-Placebo: Patients receiving tES combined with music stimulation for 2 weeks, 1 week of wash out, then sham stimulation combined with noise (placebo) for other 2 weeks.Placebo-stimulation (combined tES and music): Patients receiving sham stimulation and noise (placebo) for the first 2 weeks, then 1 week wash out, and finally tES and music stimulation for other 2 weeks.Music-placebo: Patients receiving music stimulation and sham stimulation for 2 weeks, 1 week of wash out, then sham stimulation and noise (placebo) for another 2 weeks.

**Fig 1 pone.0304642.g001:**
[figure not shown]
Study flow diagram displaying interventions and assessments.

For the treatment condition, music stimulation, lasting overall around 30 minutes, will be provided by headphones for two weeks in a row every day (except weekends) twice a day: in the morning and in the afternoon. In the morning only, this music-listening treatment will be preceded by brain stimulation with tES applied in the hemisphere contralateral to the lesion (position of electrodes adjusted according to clinical condition of the patient). The placebo condition will have the same temporal course of the treatment condition, but, instead of music, patients will listen to white noise for 30 minutes in the morning, and pink noise for 30 minutes in the afternoon and only during the morning sessions, sham (current induction for 10 minutes ramp up and 10 minutes ramp down) in the hemisphere contralateral to the lesion will be delivered. Between the two conditions, one week of washout is planned.

Patients who will develop relevant clinical condition, such as respiratory problems, during the period of protocol, will be excluded from the study.

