### Sample size determination

The effect size to be expected is uncertain as no study so far has implemented a combined intervention of music and electrical stimulation in DOC patients. We assume it to be in the medium-to large range (i.e., Cohen’s d between 0.5 and 0.8). We aim to achieve 80% power (*f* = 0.30) in a repeated-measures analysis of variance (*a* = 0.05, power (1-b) = 0.80) with condition as between-subject factor (tES combined with music stimulation vs. sham stimulation, and noise vs. music stimulation and sham stimulation), and time (pre-intervention, post-intervention and post-placebo), as within-subject factor. Power calculations (using G* Power 3) indicate that a valid sample size of *n* = 10 per group will result in 80% statistical power if the effect is *d* = 0.68, which is in the medium-to-large range. This results in a total sample size of *n* = 30.

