### Data analysis

The SPSS 23.0 statistical software will be used for the data analysis. All the statistical hypotheses will be tested by two-side test, with statistically significant test level set at 0.05 and the confidence interval estimation to 95%.

The aim of our study is to evaluate the effects of the treatments in the various patient groups on the primary and secondary outcomes. Descriptive analysis of the data will allow us to identify the characteristics of the groups. Comparison of demographic and clinical characteristics of the groups will be performed using one-way ANOVA for continuous variables and the Chi-square test for categorical variables. Considering the crossover and longitudinal aspects, primary analyses will focus on behavioural changes at group level, comparing the treatments. Moreover, at the individual level, we will analyse the differences between pre-treatments and post treatments data.

As for the primary outcomes, we will measure the effects of the intervention on the following measures (two neurophysiological and two clinical and behavioral): (i) power spectra of frequency band extracted from the EEG recordings; (ii) auditory evoked responses, extracted from the EEG recordings; (iii) behavioural responses of DOC patients, measured through CRS-R.

Baseline characteristics and carryover effect will be analysed between the three sequences using ANOVA and chi-square test. By including the order of intervention as a covariate, we aim to determine whether the sequence in which participants receive the interventions impacts the observed outcomes. To assess the presence and magnitude of the washout effect, we plan to incorporate appropriate statistical methods into our analysis, such as comparing outcomes during the washout period to those observed during active treatment phases. To this end, we will use repeated measures ANOVA considering time (before, during, and after the washout) as the independent variable, with behavioral measurements as the dependent variables.

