For the secondary outcome we will measure the effects of the treatments on caregivers’ depression, anxiety, psychophysiological symptoms, grief, strain and quality of life in order to evaluate the effectiveness in reducing the caregiver’s burden and psychological distress. Repeated-measures analysis of variance, as well as post-hoc paired *t*-tests will be conducted to assess the effects of the treatments over time on N1, P1, and P2 amplitudes and latencies, as well as level of consciousness. All these primary outcome variables will be analysed separately, using parametric or non-parametric tests for continuous and categorical variables respectively.

For the behavioural outcome, we expect an improvement of level of consciousness, as measured by CRS-R.

For the caregiver’s burden, we expect a positive effect of this new treatment protocol on caregiver’s wellbeing, with a decrease of psychological distress.

For neurophysiological outcome measures, we expect to obtain in DOC patients an increased EEG power spectrum in slow frequency bands, following a previous study [67] showing a generalized slowing in the theta or delta range associated with a significantly diminished α power. Power spectrum analysis is one of the standard methods used for quantification of the EEG. The power spectrum, namely the power spectral density, reflects the ‘frequency content’ of the signal or the distribution of signal power over frequency [68].

For the computation of the auditory evoked responses, the average EEG will be measured time-locked to the sound onset events in the music stimuli, after rejecting any residual noise exceeding 100 μV. P1 (fronto-central positive potential with ~50 ms latency), N1 (fronto-central negative potential with ~100 ms latency), and P2 (fronto-central positive potential with ~200 ms latency) amplitudes and latencies will be measured at the Fz and Cz electrodes [69], and compared pre- and post- intervention.

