To reach the goal of obtaining the above-described neurophysiological outcome measures, we will first pre-process the EEG data as follows. Data will be filtered to remove low frequencies not originating from the brain and to control for interference of the electric current, by means of a generic FIR filter, set up as a bandpass filter, with low cut-off at 0.5 Hz and high cut-off at 45 Hz (because of 50 Hz power line noise). Cerebral signals contaminated by artifacts will be identified and removed. Moreover, independent component analysis (ICA) will be performed. ICA algorithms will be used to detect and isolate artifacts, such as eye blinks, eye saccades, hearth, muscle, line noise, channel noise and others. In this way, the original signal will be decomposed into independent components: we will individuate and discard the components that picked up the artifacts activities and reconstruct a clear signal by using only the remaining components [70]. Further pre-processing steps will include epoch extraction, baseline removal, resampling, re-referencing to low temporal electrodes, and filtering.

To investigate whether slow neural oscillations are reduced and fast neural oscillations are increased post-treatment, the continuous EEG will first be divided into 2-seconds segments, transformed into the frequency domain with fast Fourier transform, inspected for myogenic artifact segments that will be rejected, and then averaged across the segments [71]. Any further exploratory analyses will be specified in the future publication of the findings of this study. Missing data will be treated according to Molenberghs et al. [72].

We will evaluate the music and electrical intervention effects on power spectra of frequency bands measuring EEG at rest and during music listening at T0 (pre-intervention), T1 (post-intervention) and T2 (post-placebo). To this end, we will compare the power spectra between rest and music conditions and across time. The ratio of fast (8–30 Hz, alpha and beta) to slow (2–8 Hz, delta and theta) oscillation amplitude at the midline electrodes (Fz, Cz, Pz, Oz) will be measured [70] and compared pre- and post- intervention using t-tests with cluster-based corrections of the multiple comparison problem. In the case of non-normal distributions, there will be applied mixed-effect ANOVAs or non-parametric equivalents to the parametric tests.

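### Randomised patients who fall ill are to be excluded from the study, and nothing says they stay in the analysis, so the comparison risks no longer being as randomised

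*Protocol article*

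**What the plan says.** The exclusion rule follows the description of the treatment and placebo sessions under Experimental design and procedures: "Patients who will develop relevant clinical condition, such as respiratory problems, during the period of protocol, will be excluded from the study". The protocol period covers two treatment periods and a one-week washout, so the rule acts on patients already randomised. Respiratory problems are the only example given of a relevant condition.

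On analysis, Sample size determination plans for power "We aim to achieve 80% power (*f* = 0.30) in a repeated-measures analysis of variance" with condition between patients "and time (pre-intervention, post-intervention and post-placebo), as within-subject factor". Data analysis names "Repeated-measures analysis of variance, as well as post-hoc paired" t-tests, and "The SPSS 23.0 statistical software will be used for the data analysis". Incomplete data get one sentence, "Missing data will be treated according to" a cited reference, with no method described. A mixed model appears once, in the EEG ratio paragraph, and is triggered by distribution rather than by missing visits: "In the case of non-normal distributions, there will be applied mixed-effect ANOVAs or non-parametric equivalents to the parametric tests".

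The abstract randomises 30 patients. Sample size determination treats 10 per group, 30 in all, as the valid number, so there is no allowance for exclusions. On blinding, Experimental design and procedures says patients and examiner are fully blinded, while the Discussion lists the inability to blind participants and assessors as a limitation.

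**The concern.** Randomisation protects the comparison only while patients are analysed where they were allocated. Here, removal depends on illness arising during the trial. In severe brain injury, illness is plausibly linked to the level of consciousness measured later, and its frequency could differ by condition or by period. If more ill patients are removed from one group than from another, the group that loses more looks better than it should. The criterion is open to judgement and that judgement may not be blind, which adds to the risk.

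With 10 patients per sequence, and only one sequence receiving placebo first, two or three removals in one sequence are a sizeable share of it. Because the number randomised equals the number needed, each removal also costs power.

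**Working it through.** **1. Does any passage keep excluded patients in the analysis?** The exclusion rule says they leave the study. Data analysis names no analysis set and does not mention the rule. The missing-data sentence does not say whether patients excluded for illness count as missing data. The mixed-effect option depends on non-normality. So the passages are left unreconciled.

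**2. The plan's own sample size.** Inputs from the article: f = 0.30, two-sided 5% level, k = 3 groups, N = 30, target power 80%. Assumed here, because the article gives no value: correlation ρ = 0.5 and sphericity. For the group-by-time interaction with m measurements:

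λ = f²·N·m/(1−ρ), df1 = (k−1)(m−1), df2 = (N−k)(m−1), power from the noncentral F.

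- m = 2: λ = 0.09 × 30 × 2/0.5 = 10.8, df 2 and 27, power 0.800. This reproduces the stated figure.
- m = 3, the number of time points the article states: λ = 0.09 × 30 × 3/0.5 = 16.2, df 4 and 54, power 0.887. The N needed for 80% is then 27, so this version does not reproduce 30.

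Both are carried forward.

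**3. Power after exclusions.** No rate is stated; 10–30% is an assumed range.

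| Excluded | N left | Power, m = 2 | Power, m = 3 | Randomised to end with 30 |
|---|---|---|---|---|
| 0% | 30 | 0.800 | 0.887 | 30 |
| 10% | 27 | 0.748 | 0.844 | 30/0.9 → 34 |
| 20% | 24 | 0.686 | 0.786 | 30/0.8 → 38 |
| 30% | 21 | 0.613 | 0.714 | 30/0.7 → 43 |

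Randomising more patients would restore power but would not remove the selection.

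**4. Possible bias, illustration only.** Suppose ill patients end 0.8–1.0 SD lower. The disadvantage removed from view by exclusion is the difference in event rates times that deficit:

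- 20% vs 10%: 0.10 × 0.8 to 0.10 × 1.0 = 0.08 to 0.10 SD.
- 30% vs 10%: 0.20 × 0.8 to 0.20 × 1.0 = 0.16 to 0.20 SD.
- Equal rates: 0.

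A small simulation (two parallel arms of 10, no true effect, SD 1, illness linked to poorer outcome, all inputs assumed) agreed. At equal rates of 10% or 20% there was no bias beyond simulation noise and type I error was about 5%. At 30% vs 10% the bias was 0.17–0.23 SD with type I error of 6–8%. Both calculations treat the groups as parallel arms, so they fit the between-sequence comparison at T1 more closely than the within-patient contrasts.

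**The case against.** The strongest reply is that the sentence sits among the procedures and may mean only that participation ends. Definition of analysis sets is commonly left to a fuller document that is not shown here. That is fair as far as it goes, and the article can be read that way. But it does state an exclusion from the study, and a later plan that kept these patients would have to depart from or reinterpret that sentence.

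Four stronger readings are tempting, and the documents do not support them:

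- *The ANOVA is restricted to complete patients.* No passage says so. A classical repeated-measures ANOVA drops a patient who lacks a time point, but the article gives a missing-data rule by citation. That rule could involve imputation and cannot be judged here.
- *The exclusion hides harm.* Data monitoring and management requires adverse events to be reported on a form. The events would be absent from the outcome comparison, not from the safety record, though nothing says they will be shown by condition.
- *A crossover needs equal sequence sizes.* It does not. With adjustment for period, unequal sizes cost precision. The issue is selection.
- *The comparison is certainly biased.* That requires exclusion to be related to outcome and to differ between groups. No event rate is given, and balanced exclusion produced no bias.

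The power figures also need care. With three measurements, 20% exclusion leaves 79%, close to the stated target. A within-patient comparison in the two reversed sequences at d = 0.68 would fall from 82% to 72% with 16 instead of 20 patients. The plan names no such analysis and does not define d that way, so nothing rests on that figure. The sample-size extension in the Discussion is tied to a smaller effect than predicted, not to exclusions.

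**Conclusion.** The point holds as a stated rule that needs correcting, together with a contradiction on blinding that makes it harder to dismiss. Randomised patients are to be excluded for an illness arising after randomisation, by an undefined criterion, and no passage keeps them in the analysis or links the rule to the handling of missing data. If the rule is carried into the analysis and exclusions differ between sequences, the comparison risks no longer being as randomised.

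The bias cannot be sized from the article. The 0.08–0.20 SD range is the product of assumed event rates and an assumed deficit, and it vanishes when exclusion is balanced. The loss of power is firmer but still rests on an assumed correlation of 0.5 and an assumed 20% loss: 80% to 69% under the version that reproduces the stated N, 89% to 79% under the three time points the article describes. This should be changed before the analysis; it does not invalidate the design.

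**What to change.** Reconcile the exclusion sentence with Data analysis by separating two things it now joins. Ending the intervention is a clinical decision and is not addressed here. For the analysis, the text could read: all randomised patients are included in the primary analysis in their randomised sequence; T1 and T2 assessments are collected where possible after any such event; the events are tabulated by condition.

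Use all available visits, for example with a linear mixed model (condition, period, T0 value, random patient effect), which SPSS offers, in place of a repeated-measures ANOVA that in its classical form drops patients with a missing time point. Say how this fits with the cited missing-data method. Report the analysis without these patients as a sensitivity analysis. Reconcile the two statements on blinding, so that the reader knows whether these events are judged with knowledge of the group.

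The cost is a change of wording, follow-up of a few patients at visits already planned, and some added variability from assessing ill patients. The mixed model also relies on missing visits being explained by the observed data. Including assessments made during illness means the primary result answers what happens to patients as allocated, illness included, and the text should say so.

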### Neurophysiological, neuropsychological and clinical primary outcomes

For obtaining the neurophysiological primary outcome measures, we will compute the power spectra of frequency bands from continuous EEG to assess the residual neuroplastic processes existing in DOC state, and we will then evaluate the putative modulation of these processes by the combined intervention of music and brain stimulation in a randomized cross-over design. EEG data will be acquired using a Galileo Mizar Plus medical device including 26 monopolar electrode channels, 16 bipolar electrode channels and 10 additional channels used for EEG recordings.

For the EEG measures, we will use the following paradigms:

Rest for 10 minutes with annotation on whether patients keep eyes open or closed for measuring the power spectra of frequency bands from the continuous EEG.Free listening to the morning musical playlist as used in the music stimulation condition for measuring the power spectra of frequency bands and the evoked N100 responses from the continuous EEG.

For assessing the clinical conditions of DOC patients, the following scales will be used.

Glasgow Outcome Scale–Extended (GOS-E) [53]: A global scale for functional outcome that rates patient status in eight categories according to the disability.Coma Recovery Scale—Revised (CRS-R) [54]: A tool which includes the current diagnostic criteria for coma, vegetative state, and the MCS, and allows the patient to be assigned to the most appropriate diagnostic category.Disability Rating Scale (DRS) [55]: A scale that evaluates the functional changes in a rehabilitation setting. The DR Scale consists of 8 items divided into 4 categories: Arousal and awareness; cognitive ability to handle self-care functions; physical dependence upon others; psychosocial adaptability for work, housework, or school.Rancho Levels of Cognitive Functioning (LCF) [56]: A scale that assesses cognitive functioning in post-coma patients, classifying them in one of eight level: No response; Generalized; Localized; Confused-agitated; Confused, inappropriate, non-agitated; Confused-appropriate; Automatic-appropriate; Purposeful-appropriate.

### Psychological and clinical secondary outcomes

We will also evaluate the impact of our intervention on caregiver’s burden and psychological distress by means of the following questionnaires for caregiver’s patients:

Beck Depression Inventory-II [57, 58]: A self-administered questionnaire to assess severity of depressive symptom, composed by 21 items to be evaluated on a 0–3 scale;State-Trait anxiety inventory [59, 60]: A self -reported questionnaire to assess level of anxiety, both state and trait anxiety;Psychophysiological Questionnaire/reduced form (CBA 2.0) [61]: A questionnaire composed by 30 items to assess the stress level and the frequency of subject’s psychophysiological reactions;Prolonged grief disorder-12 [62, 63]: A questionnaire to evaluate the presence of separation distress and cognitive, behavioural or emotional symptoms at least for six months after the disease onset of a loved person;Family strain questionnaire [64]: A questionnaire to assess perceived caregiving related problems;World Health Organization–Quality of Life [65, 66]: A questionnaire evaluating QOL in four domains: physical, psychological, social and environment relations.

